### Outcome measures

The primary outcome measure is the Oxford Shoulder Score (OSS) assessed at 6, 12 and 24 months [11]. The Oxford Shoulder Score is a condition-specific questionnaire providing a total score based on the patient's subjective assessment of pain and activities of daily living (ADL) impairment. Consistent with recent developments, the range of available scores is 0 (worst) to 48 (best) [12]. The OSS contains 12 items, each with 5 categories of response. It has been shown to correlate well with both the professionally-endorsed Constant Score [13] and the SF36 assessment, and to be sensitive to clinical change at six months after surgical intervention [14]. It has been demonstrated to be consistent, reproducible and valid in a UK population [11]. This questionnaire will be administered by post for self-completion by the trial participant without need for an examination and thus avoids the requirement for follow-up visits to the clinic for assessment. To improve compliance, reminders will be sent and patients will be offered the option of completing the questionnaire via a telephone call. We will also send pre-notification letters and use unconditional incentives; both have been shown to be effective at improving response rates [15].

Secondary outcomes are:

• Surgical complications; including shoulder dislocation, failure of implant, proven wound infection (purulent discharge plus positive bacteriology or need for revision due to infection), septicaemia (clinical evidence of systemic infection plus positive blood cultures).

• Early medical complications, i.e. chest infection, confirmed MI or stroke (confirmed by senior clinician), treated DVT, treated pulmonary embolism and other serious event.

• Mortality, subsequent referral for operation or substantive treatment.

• The SF12 and Euroqol (EQ-5D) to collect general health status data (at 6, 12 and 24 months).

#### Data for economic evaluation

Prospective cost data on trial participants include costs incurred in hospital and subsequently. Thus, time spent in theatre and hospital consumables will be collected. Health utility data will also be obtained from the EQ-5D collected at 3, 6, 12 and 24 months [16]. Information for estimating NHS and societal costs will be collected from the trial participants at each follow-up.

We will collect data on the actual procedures performed, including anaesthesia, and interventions provided and the experience of operators/care providers (according to grade). We will collect these data for all trial participants.

### Data collection

We shall aim to make the trial processes as simple as possible in order to minimise the work entailed at the participating centres. As far as possible, we hope to achieve complete follow-up of all randomised patients.

#### Baseline data

Basic information including key baseline characteristics will be collected for all potentially eligible patients (i.e. those meeting the trial inclusion criteria) who are found not to be eligible.

Additional data on patient preferences, surgeon's advised treatment and the agreed treatment will be obtained for patients who do not consent to trial participation.

For consenting patients, we will collect data on ethnicity, education, employment, previous fractures, shoulder dominance, injury mechanism, smoking, diabetes, treatment preference, current health status (EQ-5D), GP name and surgery and the patient's contact details.

#### Description of treatment

##### Surgical methods

Brief details of the actual surgery and procedures used will be recorded by the surgeon, or assigned deputy, following the operation. Also prescribed rehabilitation.

##### Non-surgical methods

Brief details of the prescribed non-surgical treatment will be recorded by surgeon, or assigned deputy. Also prescribed rehabilitation.

#### Collection of hospital outcome data - before hospital discharge

Centres will be required to complete data forms detailing:

• Clinical outcomes including surgical complications and early medical complications

• Resource use: the data on hospital costs will be collected using a cost proforma designed for the trial.

• Substantive deviations from prescribed treatment and rehabilitation

• Patient destination after hospital discharge

#### Long term follow-up

One and two year follow-up forms from centres

Forms to notify mortality or subsequent surgery for completion and return at any time will be made available for the completion by centre staff. Forms for completion will be sent at 1 and 2 year follow-up - it is likely that all the data for these can be gleaned from the hospital records for these patients.

#### Follow-up patient questionnaires: 3, 6, 12 and 24 months post trial recruitment

A short questionnaire including the EQ-5D and brief questions on the number of consultations of NHS care providers (GPs, physiotherapists, district nurses etc), hospitals attendances, use of private healthcare and days lost from work or other normal activities will be sent together with a covering letter by the YTU to all participants at three months. Reply paid envelopes will be included. Reminders will be sent after 2 and 4 weeks

Full questionnaires, together with covering letters and reply paid envelopes, will be sent by the YTU to all participants at six, 12 and 24 months after recruitment. These include the Oxford Shoulder Score, EQ-5D and SF12, all of which are self completion questionnaires. As at 3 months, brief questions on the number of consultations of NHS care providers (GPs, physiotherapists, district nurses etc), hospitals attendances, use of private healthcare and days lost from work or other normal activities will also be requested. Reminders will be sent after 2 and 4 weeks and options for completion of the questionnaires via telephone after 6 weeks. If completed over the telephone, only the Oxford Shoulder Score, EQ-5D and information on hospital readmissions will be requested. An unconditional incentive payment of £5 will be sent for the 12 and 24 month follow-ups [15].

### Radiographs

Copies of all baseline radiographs for all randomised patients will be requested for independent and blinded assessment at the end of study recruitment. Radiographs will also be reviewed by local experts on an on-going basis during trial recruitment to ensure the images are of sufficient quality for scrutiny and classification based on the Neer classification system by an independent panel of experts at the end of recruitment.

### Sample size

The primary outcome for the trial is differences in patients' subjective assessments of pain and activities of daily living (ADL) as measured by the Oxford Shoulder Score (OSS). For surgery to be worthwhile, it needs to demonstrate greater improvements in patient's subjective assessments of pain and ADL than those for conservative treatment to justify both its increased costs and the exposure to the hazards of surgery. In an observational study conducted by one of us (AR) it was found that those patients who had surgery had a 5 point differential improvement in the OSS compared with those patients treated conservatively. Given a standard deviation of 12 this equates to an effect size of 0.42. We propose, therefore, to design the study to observe an effect size of 0.4 at 80% power using 5% significance level, which would require approximately 200 participants. After allowing for drop-outs of 20%, we propose to recruit and randomise 250 patients (125 surgery and 125 controls). Our estimate of 20% loss from the RCT is purposefully pessimistic for sample size calculations.

#### Recruitment rate

We anticipate that recruitment for this trial will be potentially challenging. Therefore, we have set very conservative recruitment targets. Our recruitment period is 18 months. We aim to recruit between 18-20 centres. Each centre will be expected to recruit only one participant per month, though encouraged to aim higher than this. We estimate across 18 centres there will be 6066 patients (6000 is used as a working figure here) with a proximal humeral fracture over the 18 months of recruitment. Of these, 2391 (thus, 2400 is used as a working figure below) will have the fracture types suitable for inclusion into the RCT. To achieve our sample size we need to recruit only 11% of these patients.

#### Loss to follow-up

We anticipate that the main reason for loss to follow-up will be mortality. We will follow up patients assiduously using postal questionnaires and in the event of non-response we will contact their GP to ascertain whether it is appropriate to contact the patient and, if so, their address.

### Statistical analysis

All of the analyses will use the intention-to-treat principle. Consequently, any patients who cross over from either study arm will be analysed as per their randomisation status. The primary outcome is the Oxford Shoulder Score (OSS). The difference between the two treatment groups will be compared over all follow-up assessments (i.e. 6, 12 and 24 months) using a repeated measures model. The model will include terms for treatment, follow-up time, and also adjust for type of fracture, age and gender (as older people and women are more likely to sustain these fractures). Because participants are clustered by surgical centre there is a theoretical possibility that there may be a 'surgeon' effect. We will therefore repeat the primary analysis using appropriate statistical techniques (robust standard errors) to account for the clustering of patients within surgeon. The anonymity of individual surgeons and centres will be preserved for all analyses and there will be no presentation or comparisons of the treatment results from individual centres or surgeons. Subgroup analyses based on the Neer classification system are planned to assess the effectiveness of treatment for the different fracture groups (2 part surgical neck; 3 part including surgical neck and 4 part fractures; fractures not meeting the Neer classification displacement criteria). The secondary outcomes will be summarised for each treatment group.

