• Concealment of treatment allocation prior to trial entry will be ensured by use of an independent telephone randomisation service, as provided by the York Trials Unit. After an initial, prespecified, period of randomisation, stratified by the presence or not of a tuberosity fracture and with a prespecified block size, randomisation will then be performed using a computer generated minimisation programme. The minimisation factors will be fractures involving either tuberosity and centre.

• We will emphasize good practice and standardised protocols and care pathways throughout, and comparable and sufficient expertise of care providers. Surgery for these types of fractures are usually carried out by consultants; this has been confirmed by an informal survey of the centres initially included in our study. We will attempt to minimise 'learning curve' issues for the surgical interventions by allowing the surgeon to use techniques with which they are familiar, but prohibiting the introduction of radically new or experimental methods during the recruitment period.

• We will encourage the prescription of comparable care, including rehabilitation programmes, such that any substantive departures from the norm would reflect the special requirements of a specific intervention. Consensus guidelines for rehabilitation for both groups have been prepared by rehabilitation specialists and were circulated for comment and input. These form part of the trial materials and we will request details of where the prescribed treatment differs substantively from the standardised protocols. (See Notes added in clarification below.)

Notes added for clarification

*1. Upon discussion, the proposed consensus guidelines for non-surgical management were considered inappropriate in the context of a pragmatic trial and the lack of evidence to inform practice. It was decided that the onus should be on the provision of good standard care and that our approach would be to indicate both verbally and in the site manual that we would anticipate initial care to comprise sling immobilisation for about 3 weeks or for as long as the treating clinician deemed necessary and active early rehabilitation. We considered that written information to advise patients during sling immobilisation was needed and should be provided to all eligible patients for the trial. We provide a generic document to be adopted by the hospital should a suitable document not already be available locally*.

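### Centre is a minimisation factor but is not in the primary Oxford Shoulder Score model; if outcomes differ between centres, the standard error will be slightly conservative

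*Protocol article*

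**What the plan says.** The section on avoiding bias describes allocation in two phases. The first is "After an initial, prespecified, period of randomisation, stratified by the presence or not of a tuberosity fracture and with a prespecified block size"; centre is not named there. The second is a computer-run minimisation: "The minimisation factors will be fractures involving either tuberosity and centre".

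Under Statistical analysis, the arms are "compared over all follow-up assessments (i.e. 6, 12 and 24 months) using a repeated measures model". The covariates are then fixed: "The model will include terms for treatment, follow-up time, and also adjust for type of fracture, age and gender". There is no centre term.

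On clustering, the same section says "Because participants are clustered by surgical centre there is a theoretical possibility that there may be a 'surgeon' effect". It continues: "We will therefore repeat the primary analysis using appropriate statistical techniques (robust standard errors) to account for the clustering of patients within surgeon". No intracluster correlation (ICC) is given for centre or for surgeon.

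**The concern.** Minimising on centre forces the arms to be nearly equal in size within each centre. Differences in outcome level between centres then largely cancel out of the treatment comparison. A model without centre does not know this: it leaves the between-centre variation in the residual and reports a standard error that still contains it. The test is then somewhat conservative, and precision that the design has bought is not used on the primary outcome.

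Centre differences are plausible here. The choice of operation is left to the surgeon, peri-operative care follows local guidelines, sling duration is at the clinician's discretion, and variation in physiotherapy is expected.

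The omission is not a detail left open for an analysis plan. The article gives a definite list, which includes two variables not used in allocation (age and gender) and leaves out one that was. The repeat analysis does not clearly close the gap. It starts from clustering by centre and then sets out to "account for the clustering of patients within surgeon", which need not be the same unit as the one minimised on.

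**Working it through.** **1. The plan's own figure.** Inputs from Sample size: effect size 0.4, power 80%, significance level 5% (two-sided assumed), drop-out 20%.

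n per arm = 2(1.960 + 0.842)²/0.4² = 98.1, so 99 per arm and 198 in total. The t-test version needs 100 per arm, 200 in total. Then 200/(1 − 0.20) = 250. The stated 200 and 250 are reproduced.

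**2. Standard error as planned.** The section says "Given a standard deviation of 12 this equates to an effect size of 0.42". The design effect of 0.4 is 0.4 × 12 = 4.8 points. With 100 per arm, SE = 12√(2/100) = 1.697.

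**3. Effect of balance within centre.** Let ICC be the share of the variance of 12² = 144 that lies between centres. With arms balanced within centres, that share drops out of the treatment difference:

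- true SE ≈ 1.697 × √(1 − ICC)
- SE reported without centre ≈ 1.697
- ratio = 1/√(1 − ICC)
- actual two-sided type I error without centre = 2[1 − Φ(1.960/√(1 − ICC))]
- power without centre = Φ[(4.8 − 1.960 × 1.697)/true SE]
- power with centre = Φ[4.8/true SE − 1.960]

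The ICC values are assumptions.

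| ICC | SE without centre | SE with centre | Excess | Type I error without | Power without | Power with |
|---|---|---|---|---|---|---|
| 0 | 1.697 | 1.697 | 0% | 5.0% | 80.7% | 80.7% |
| 0.02 | 1.697 | 1.680 | 1.0% | 4.8% | 81.0% | 81.5% |
| 0.05 | 1.697 | 1.654 | 2.6% | 4.4% | 81.4% | 82.7% |
| 0.10 | 1.697 | 1.610 | 5.4% | 3.9% | 82.0% | 84.6% |

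Worked line for ICC 0.10: true SE = 1.697 × √0.90 = 1.610. Power without centre = Φ[(4.8 − 3.326)/1.610] = Φ(0.916) = 82.0%. Power with centre = Φ(2.981 − 1.960) = Φ(1.021) = 84.6%.

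**4. Check by simulation.** There were 2,500 trials per setting, each with 200 patients, 18 centres and minimisation on centre and tuberosity. Minimisation used a biased coin of 0.9 (assumed). Each patient had one score, analysed by a linear model with treatment and tuberosity, with or without fixed centre terms.

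- ICC 0.10, no effect: without centre, the mean reported SE was 1.692 against an empirical 1.603, with type I error 3.9%. With centre, the mean SE was 1.620 and type I error 4.6%.
- ICC 0.10, effect 4.8: power was 80.1% without centre and 82.9% with it.
- ICC 0.05, effect 4.8: power was 81.0% and 82.2%.
- ICC 0.02, effect 4.8: power was 81.2% and 80.4%.
- ICC 0, effect 4.8: power was 80.2% and 79.4%. The mean SE was 1.696 without centre and 1.706 with it, so the fixed terms cost 1.706/1.696 − 1 = 0.6%.

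Each simulated power has a Monte Carlo standard error of about √(0.8 × 0.2/2500) = 0.8 points.

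**5. Robust standard errors.** When clustered on centre at ICC 0.10, the mean robust SE was about 1.60 and type I error 5.1%, so the excess width was largely removed. Power was 77.7% with a t reference on centres minus one degrees of freedom, so the power was not recovered. Clustering on surgeon was not simulated, because the article does not say how many surgeons each centre has.

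**The case against.** The strongest reply is that nothing in the trial's conclusions is at risk. The estimate is unbiased, any error is on the conservative side, and power without centre is about 80% to 82% across the assumed range. All of that stands, and it is why the point is minor.

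A reader might go further than the document allows in four ways:

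- **That the standard errors are too wide, as a fact.** This needs a between-centre ICC above zero, and the document gives none. At ICC 0 there is no excess, and fixed centre terms then do very slightly worse.
- **That the trial loses its planned power.** It does not. What is forgone is up to about 3 points above the plan, at the top of the assumed range.
- **That the mismatch covers every patient.** Centre is not named as a factor in the initial blocked period, so the argument applies to the minimised phase. Step 4 minimises all 200 patients on centre and therefore shows the upper end.
- **That clustering is ignored.** It is not. A robust standard error can correct the variance without a centre term, and clustered on centre it largely did so in the check. What remains is narrower: the planned clustering unit is surgeon, and only in a repeat analysis.

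It can also be said that the fracture-type term may already be the tuberosity factor, since the Neer groups are mentioned separately for subgroups. That is possible, and no error is claimed on it; naming the variable would settle it. Adjusting for age and gender is acceptable and changes nothing here.

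**Conclusion.** The point holds in limited form. Centre is used to balance allocation, the fixed covariate list of the primary model leaves it out, and the repeat analysis clusters on surgeon although centre is named as the source of clustering.

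If outcomes differ between centres, the primary standard error is conservative: by about 1% at ICC 0.02, 2% to 3% at 0.05 and 5% at 0.10. At most about 3 points of power are forgone. There is no bias, and the sample size of 250 is unaffected.

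The size rests on the assumed ICCs, 100 analysed patients per arm, an SD of 12, 18 centres, and one score per patient in place of the three repeated scores. The severity is minor; this is a free improvement rather than a correction of an invalid analysis.

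**What to change.** State the primary model terms as: treatment, follow-up time, tuberosity involvement as recorded at randomisation, centre (random intercept, or fixed with small centres pooled), age and gender. Otherwise, give a reason for leaving centre out.

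Keep the repeat analysis with surgeon-level robust standard errors as a sensitivity analysis. Reword the sentence before it so that the named source of clustering and the clustering unit agree.

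The cost is a line or two of text. No new data are needed, because centre and tuberosity status are already inputs to the minimisation. If centres do not differ at all, fixed centre terms widen the standard error by less than 1%.

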#### Frequency of analyses

We anticipate that there will be a single analysis at the end of the study. However, decisions about the need for interim analysis will be taken by the chair of the independent Trial Steering Committee (TSC) in conjunction with the chair of the Data Monitoring and Ethics Committee (DMEC).

#### Assessment of study recruitment and applicability

We will report the numbers of and reasons for ineligible adults (aged 16 or above) with the study fractures, we will also report the numbers of and reasons for the non-inclusion of potentially eligible patients. We will compare the baseline characteristics, patient preferences with those of randomised patients.

### Economic evaluation

An economic analysis will be taken from the perspective of the UK National Health Service and Social Services. The horizon for the baseline analysis will be two years. However, we will model any potential benefits forward to 5 years and an average lifetime in a sensitivity analysis.

Health benefits for the economic analysis will be measured in terms of quality adjusted life years (QALYs). Health utility values for individuals with displaced proximal humeral fractures will be estimated using the Euroqol (EQ-5D) questionnaire. QALYs will be calculated for each patient using the area under the curve defined by her/his EQ-5D scores over the two-year follow-up period and adjusted by the Kaplan Meier estimates of patients' survival over the same period of time. Given the horizon for the analysis is longer than a year a discount rate of 1.5% will be applied to health benefits [17].

Resource use and clinical data will be collected for all trial participants. Information regarding total volume of resources used in the treatment (conservative/surgical) and rehabilitation procedures will be recorded for each patient. Unit cost will then be applied to estimate the total cost per patient. To account for the censored nature of cost data, the Lin method will be used to estimate the mean average total cost per treatment arm [18]. Non parametric bootstrapping techniques will be used to estimate 95% confidence intervals for the mean differential cost between conservative and surgical treatment [19]. Total cost will be discounted using a 6% annual discount rate [17].

Health benefits and mean average total costs associated with each of the trial arms will be combined in a cost-utility analysis, incremental costs per quality ratios will be computed comparing the conservative and surgical treatment interventions for adult patients with a displaced proximal humeral fracture. Multilevel modelling will be used to explore potential variations in treatment effect and costs between health professionals [20].

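### Baseline EQ-5D is collected before randomisation, but the plan does not say that it starts the QALY curve or adjusts the QALY difference, which is a free gain in clarity and precision

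*Protocol article*

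**What the plan says.** All references are to the protocol article.

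- **Baseline data.** The items recorded for consenting patients include "treatment preference, current health status (EQ-5D), GP name and surgery". The section on practical arrangements for recruitment and allocation has the baseline form completed before the randomisation service is contacted, so this value precedes allocation.
- **Data for economic evaluation.** "Health utility data will also be obtained from the EQ-5D collected at 3, 6, 12 and 24 months". Baseline is not in this list.
- **Economic evaluation.** "QALYs will be calculated for each patient using the area under the curve defined by her/his EQ-5D scores over the two-year follow-up period". The one adjustment named is that QALYs are "adjusted by the Kaplan Meier estimates of patients' survival over the same period of time". Baseline utility is not mentioned.
- **Outcome measures.** "The primary outcome measure is the Oxford Shoulder Score (OSS) assessed at 6, 12 and 24 months". There is no baseline OSS.
- **Statistical analysis.** For the primary outcome, "The model will include terms for treatment, follow-up time, and also adjust for type of fracture, age and gender". EQ-5D is not among these covariates.

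**The concern.** Three sections that should fit together leave a gap. One collects a baseline utility, one lists the utility time points without it, and one calls for an area over two full years. If the list of time points were taken as complete, the first three months would have no starting value, and the analyst would have to choose a convention after the data are in.

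The second issue is precision. An area that starts at baseline contains the baseline value and is also correlated with it through the later scores. Given an observed baseline difference between the arms, the unadjusted QALY difference is expected to move in the same direction. Regression on the baseline value removes that part and narrows the interval. Incremental QALYs are one of the two quantities in the cost-utility ratio, so their precision matters to one of the trial's two stated aims.

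**Working it through.** **The plan's own figure.** With effect size 0.4, two-sided 5% (sidedness is not stated) and 80% power, n per arm = 2(1.96 + 0.84)²/0.4² ≈ 98, rounded up to 99, or 198 in total. The plan's 200, divided by 0.8 for drop-out, gives 250. The stated sample size reproduces, and this point does not affect it.

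**Assumptions for the QALY calculation.** The article gives no EQ-5D SD or correlation. Assumed: a common SD of 0.30 at each time (range 0.20 to 0.35); 100 analysed per arm; correlation r of baseline with each later score from 0.1 to 0.5; correlation 0.6 between later scores. Discounting and deaths are ignored.

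**Curve weights.** The trapezium rule at 0, 0.25, 0.5, 1 and 2 years gives 0.125, 0.25, 0.375, 0.75 and 0.5, which sum to 2.

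**Chance baseline difference.** SE = 0.30 × √(2/100) = 0.042. An imbalance of 0.05 is 0.05/0.0424 = 1.18 SE, which is exceeded in one direction or the other in about 24% of trials.

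**Slope of QALY on baseline.** Slope = 0.125 + 1.875r, where 1.875 is the sum of the later weights.

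**QALY variance, in units of SD².** The later scores contribute 0.4 × 1.0156 + 0.6 × 1.875² = 2.5156, where 1.0156 is the sum of their squared weights. Baseline adds 0.0156, and the cross term is 0.46875r. The proportion of variance removed by adjustment is slope² divided by the total.

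| r | Slope | QALY shift for imbalance of 0.05 | Total variance (SD²) | SE unadjusted | Variance removed | SE adjusted |
|---|---|---|---|---|---|---|
| 0.1 | 0.3125 | 0.016 | 2.578 | 0.068 | 4% | 0.067 |
| 0.3 | 0.6875 | 0.034 | 2.672 | 0.069 | 18% | 0.063 |
| 0.5 | 1.0625 | 0.053 | 2.766 | 0.071 | 41% | 0.054 |

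**Sensitivity.** The slope and the percentage removed do not depend on the SD. A 1-SE imbalance shifts incremental QALYs by 0.009 (SD 0.20, r = 0.1) to 0.053 (SD 0.35, r = 0.5). If the correlation between later scores is c, their contribution is 1.0156 + 2.5c. At r = 0.3, the variance removed is then 0.4727/2.172 = 22% for c = 0.4 and 0.4727/3.172 = 15% for c = 0.8.

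**Direct weight of baseline.** Its own weight is 0.125 of 2 years. At SD 0.30, a 1.96-SE imbalance enters directly as only 0.125 × 0.083 = 0.010 QALY. The rest of any shift comes through correlation with later scores.

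**Primary OSS model.** With 100 per arm and d = 0.4, power = Φ(0.4√50/√(1 − r²) − 1.96). Here r is the correlation of baseline EQ-5D with OSS that remains after the listed covariates. Power is 80.7% at r = 0, 81.1% at 0.1, 82.3% at 0.2 and 84.3% at 0.3.

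**The case against.** The strongest reply is that the gap is one of silence. A reader might infer that baseline EQ-5D is left out of the QALY calculation, but the article does not say so. A two-year area needs a starting value and the baseline score is the obvious one. The listed time points match the postal questionnaire schedule and may only describe follow-up collection. Regression adjustment is also a detail that a condensed article can leave to an analysis plan. These arguments stand. They reduce the point to an improvement on the methods as stated, and they rule out a charge that data are discarded. They do not remove the mismatch between the sections, which lies within the article. Nor do they change the fact that survival is the only QALY adjustment named in an otherwise detailed section.

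A second reply is that chance imbalance under randomisation is random error, already reflected in the confidence interval. That is correct, and it would be wrong to call this bias. It does not answer the precision argument: given an observed imbalance, the unadjusted estimate is displaced in a predictable direction, and its interval is wider than necessary.

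A third reply is that leaving EQ-5D out of the OSS model is not a mistake. This also stands. EQ-5D is a different, generic instrument, recorded soon after an acute fracture. The article gives no correlation with later OSS, and the sample size does not rely on one.

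**Conclusion.** The point holds as a costless improvement. The article collects a pre-randomisation utility, does not list it as a utility time point, and names no adjustment of QALYs for it. Under the stated assumptions, adjustment would remove about 4% to 41% of QALY variance. An imbalance of 0.05 would shift incremental QALYs by about 0.016 to 0.053, that is, from about a quarter to three quarters of a standard error. At the low end of the correlation range there is almost nothing to gain. The SD and every correlation are assumptions.

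Two further inferences are tempting and unsupported. One is that imbalance would reverse the sign of the incremental QALYs: the article gives no expected QALY difference against which to judge this. The other is that the arms differ most in the first three months: the article gives no utility data for any period. For the OSS model, there is at most a missed gain of unknown size, from nil to a few percentage points of power at correlations up to 0.3.

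**What to change.** 1. Under Data for economic evaluation, add baseline to the utility time points, so that they read baseline, 3, 6, 12 and 24 months.
2. Under Economic evaluation, state that each patient's curve starts at the baseline EQ-5D, and that incremental QALYs are estimated by regression on arm with baseline EQ-5D as a covariate. If a separate analysis plan already says this, a reference to it is enough.
3. Optionally, prespecify baseline EQ-5D as a covariate in the primary OSS model, alongside fracture type, age and gender. This must be fixed before any outcome data are seen by arm.

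The cost is wording only. The data are already being collected before allocation, and no sample size or schedule changes.
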